### Intervention

Eligible patients will receive Proxalutamide (300 mg, Kintor Pharmaceuticals Ltd., Suzhou, China) plus standard of care. Proxalutamide will be administered orally once daily at the same time each day (± 2 h according to medication scheduling). The duration of the study treatment will last for 7 days and can be extended to 14 days at the discretion of the investigator.

Any dose that is missed and delayed may be administered as soon as possible on the same calendar day. When it is almost time for the next scheduled dose (within 4 h), we recommend skipping the missed dose and taking the next dose instead. The missed dose will not be made up if it is not given on the same calendar day.

Use of antipyretic medications (eg, paracetamol) or other adjunctive medications (eg, vitamins) is allowed before enrollment. Use of the following drugs is allowed during the trial period: treatment drugs against adverse events as well as underlying conditions (used stably for at least 3 months); oral contraceptive; convalescent plasma from recovered COVID-19 patients; anti–SARS-CoV-2 monoclonal antibodies; corticosteroids. Moreover, participants are advised to avoid the consumption of grapefruit, carambola, bigarade, or their juice, which belongs to CYP3A4 inhibitors and can increase exposure to proxalutamide. Allowable drugs for severe or critically ill patients with COVID-19 are administered based on investigators’ clinical judgment and clinical practice guidelines [20].

Discontinuance criteria of treatment are as follows: (1) If participants are tested negative for SARS-CoV-2 by RT-PCR assay or Ct values > 35, and repeated testing is still negative or Ct values > 35 after 24 h, the treatment will be discontinued by the investigator; (2) If grade 3–4 drug-related adverse events (AEs) occur during treatment, proxalutamide will be permanently discontinued.

It is important for the patient to fully understand the importance of conducting the trial, medicine administration on time, and follow-up on schedule during the trial for enhancing patient adherence. The subjects will be required to take the medicine according to the regulations, fill in the patient diary card on time, and attend the follow-up as required.

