### Study endpoints

The primary endpoint of this study is 30-day all-cause mortality. Secondary outcomes include the following:(1) 60-day all-cause mortality;(2) The proportion of clinical deterioration, which is defined as the need within 30 days after administration for admission to the intensive care unit or invasive mechanical ventilation/ extracorporeal membrane oxygenation (ECMO), or all-cause mortality;(3) Mean change in clinical status using the 8-point-ordinal-scale from day 1 (baseline) to day 15 and day 22 (optional);(4) Time to sustain clinical recovery (determined using an 8-point ordinal scale);(5) Percentage of subjects reaching sustained clinical recovery (determined using an 8-point ordinal scale) on days 5, 8, 15, and 22 (optional);(6) Mean change in the Acute Physiology and Chronic Health Evaluation II (APACHE-II) scores from day 1 (baseline) to days 15 and 22 (optional);(7) Changes in oxygenation index measured by blood gas analysis or blood oxygen saturation from day 1 (baseline) to days 3, 5, 8, 15, and 30 (optional);(8) Changes in chest CT scan (optional) from baseline to day 8 or 15;(9) Percentage of subjects confirmed negative for SARS-CoV-2 RT-PCR by nasopharyngeal (NP) swab on days 3, 5, 8, 15, and 30 (optional);(10) Change in Ct values of SARS-CoV-2 RT-PCR on days 3, 5, 8, 15, and 30 (optional);(11) Safety assessments (eg, AEs, serious AEs, and abnormal laboratory data) from the time of SARS-CoV-2 RT-PCR turned negative to day 30.

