## Discussion

COVID-19 is a new and poorly understood disease that posed a huge challenge to global public health. Most patients with COVID-19 have mild symptoms, but some patients rapidly develop severe and critical illnesses, and the mortality of critically ill patients with COVID-19 is high [28]. Previous reports revealed that androgen-mediated expression of ACE-2 and TMPRSS2 related to the degree of severity and mortality of COVID-19 disease [29–31]. Proxalutamide as a novel potent AR antagonist has been shown to downregulate the expression of ACE2 and TMPRSS2 in lung cancer cells, and also accelerate viral clearance in mild to moderate patients with COVID-19 [32]. But the efficacy of proxalutamide treatment for severe and critically ill COVID-19 patients is unclear. Therefore, a single-arm, open-label, prospective exploratory trial is designed to investigate the efficacy and safety of proxalutamide in the treatment of severe and critically ill patients with COVID-19 for the first time.

This trial has several strengths. First of all, this is the first prospective study of proxalutamide in the treatment of severe or critically ill patients with COVID-19 in China. Currently several clinical trials of proxalutamide in COVID-19 are focused primarily on mild to moderate patients, all patients without the severity of illness, or mechanism of action for proxalutaminde treatment [16, 33, 34]. Our study will provide sufficiently strong evidence to guide the treatment of severe or critically ill patients with COVID-19. Secondly, there are no specific therapeutic agents or vaccines for COVID-19 available. This trial study on androgen receptor antagonists which is a novel therapeutic target in COVID-19, inhibiting SARS-CoV-2 infection by regulating ACE2 and TMPRSS2. It may provide a basis and reference for other androgen receptor drugs with similar mechanisms in COVID-19. Moreover, this study allows patients to use convalescent plasma from recovered COVID-19 patients, SARS-CoV-2 monoclonal antibody therapy, and corticosteroid during the treatment period. Under these conditions can represent the real world of the treatment of COVID-19 as accurately as possible.

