Despite the above strengths, there are still some limitations in the present study. Firstly, our sample size was small and the trial was conducted at one center. However, as the COVID-19 pandemic is a sudden and temporary event, the center for accepting and treating severe or critically ill patients with COVID-19 is limited and temporally, meanwhile, the number of recruited severe or critically ill patients at clinical centers may be low. Secondly, this trial did not include a control group, therefore, reducing the generalizability of our results. Because there is no approved effective conventional treatment for patients with severe or critical COVID-19. Given the ethical considerations of protecting the maximum benefits of participants and the objectives (rapid discovery of proxalutamide efficacy) of this investigator-initiated clinical trial, no control group was recruited for this study. Randomized controlled trials will continue to be conducted in the future to assess the effect of proxalutamide. Thirdly, this is an open-label trial, considering severe or critically ill patients with COVID-19 may deal with invasive treatment delivered in the ICU (including ECMO), which is undoubtedly more difficult or impossible to conduct a blinded trial. But blind will be maintained for all other members of the clinical and research team, such as statistical staff, to minimize bias.

In summary, the present trial is the first to investigate the efficacy and safety of proxalutamide in severe or critically ill patients with COVID-19. The findings of this study might provide convincing evidence regarding the efficacy and safety of proxalutamide on severe or critically ill patients with COVID-19.

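### Permitted anti-SARS-CoV-2 antibodies and plasma cannot be separated from proxalutamide in the PCR and Ct endpoints, yet the Discussion presents this co-treatment as a strength

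*Protocol article*

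**What the plan says.** All references are to the protocol article.

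- **Intervention.** Patients receive proxalutamide on top of standard of care. The drugs allowed during the trial include "convalescent plasma from recovered COVID-19 patients; anti–SARS-CoV-2 monoclonal antibodies; corticosteroids". The stated condition is the investigators' "clinical judgment and clinical practice guidelines"; no limit on timing or number of patients is given.
- **Study endpoints.** Secondary outcome (9) is "Percentage of subjects confirmed negative for SARS-CoV-2 RT-PCR by nasopharyngeal (NP) swab on days 3, 5, 8, 15, and 30 (optional" and outcome (10) is "Change in Ct values of SARS-CoV-2 RT-PCR on days 3, 5, 8, 15, and 30 (optional". The day-30 measurement is optional.
- **Intervention, first discontinuance criterion.** After a negative test or a Ct above 35, if "repeated testing is still negative or Ct values > 35 after 24 h, the treatment will be discontinued by the investigator". The Follow-up and data collection section defines viral clearance during treatment by the same pair of results.
- **Statistical analysis.** Secondary endpoints are analysed according to variable type. Co-treatment is not mentioned.
- **Table 2.** Concomitant medication is reviewed at baseline, daily until discharge, and on days 15, 22 and 30.
- **Discussion, strengths.** "this study allows patients to use convalescent plasma from recovered COVID-19 patients, SARS-CoV-2 monoclonal antibody therapy, and corticosteroid during the treatment period". The next sentence gives the reason: "Under these conditions can represent the real world of the treatment of COVID-19 as accurately as possible". The same paragraph says the study will yield evidence strong enough to guide treatment.
- **Discussion, limitations.** "this trial did not include a control group, therefore, reducing the generalizability of our results".

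**The concern.** Monoclonal antibodies against SARS-CoV-2 and convalescent plasma are directed at the virus, and outcomes (9) and (10) measure the virus. In a randomised trial, use of such agents would tend to balance between arms. Here nothing balances it, so any of them that works moves (9) and (10) in the direction that will be read as benefit of proxalutamide.

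The stopping criterion adds a second problem. The result that counts as clearance also ends dosing, so exposure to proxalutamide depends on the outcome. A patient who clears because of another agent takes fewer doses and still counts as a clearance under proxalutamide.

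What is at stake is the reading of the viral results. The Discussion offers the permission as an advantage and describes the missing control group as a matter of generalizability. The loss is one of attribution, and the text does not say so.

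**Working it through.** The plan gives no expected clearance rate, reference rate or success criterion for outcomes (9) and (10), so there is no figure of its own to reproduce. Its sample size calculation concerns mortality and does not bear on this point.

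**1. Form of the bias.** Let f be the fraction of patients given an antibody or plasma before the swab, r0 the probability that these patients would be negative without it, and r1 the probability with it.

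Shift in the reported proportion = f × (r1 − r0)

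The documents give none of f, r0 or r1, so the shift cannot be computed.

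**2. What can be bounded.** Each co-treated patient can change the count of negatives by at most one. With k co-treated patients among n with a result at that visit, the shift is at most k/n. If all 64 recruited patients have a result, each co-treated patient accounts for at most 1/64 = 1.6 percentage points; with fewer results, the share per patient is larger. This is a ceiling, not an estimate. It shows why k has to be reported: if k is near zero, the issue disappears.

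**3. Stopping criterion against the swab schedule.** Inputs: swabs nominally on days 3, 5 and 8; confirmation after 24 h; planned treatment of 7 days, extendable to 14.

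- First negative on day 3, confirmed on day 4: dosing ends after 3 or 4 daily doses, depending on whether the day-4 dose precedes the result, out of 7 planned.
- First negative on day 5, confirmed on day 6: 5 or 6 of 7.

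This holds for anyone who clears early, whatever the cause. The documents do not say how many co-treated patients, if any, follow this path.

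**4. Passages side by side.** Intervention allows virus-directed agents; Study endpoints measures virus; the design has one arm; the Discussion counts the allowance as a strength. The first three together mean that a change in PCR or Ct in a co-treated patient cannot be assigned to proxalutamide. The fourth conflicts with that.

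**5. Are the data there?** Table 2 has medication reviewed daily in hospital and at three later visits, so the start of an agent relative to each swab should be recoverable. For agents given before day 1, this assumes that the baseline review records them.

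**The case against.** **Silence about the analysis is not a fault here.** The article condenses a fuller document, and tables by concomitant medication are commonly left to an analysis plan, which is not shown. A reader might infer that the co-medication data will go unused; the article does not say that. This objection stands, and the missing table alone would not be a finding. It does not reach the Discussion, whose wording an unseen analysis plan would not correct.

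**Background care is part of the regimen.** Guideline care in severe illness is a legitimate pragmatic choice, and the treatment is defined as proxalutamide plus standard of care. This stands too. The permission is not an error and is not unrestricted, since it is tied to judgment and guidelines. The fault lies in what is claimed from it.

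**The root cause is the single arm.** Even with no antibody use, natural clearance to day 30 could not be separated from a drug effect. The limitations admit the missing control group and say that randomised trials will follow. This stands as a limit on the fix: separating co-treated patients removes one avoidable source of bias and leaves the rest.

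**Mortality.** A reader might infer that co-treatment also undermines the comparison of 30-day mortality with 12%. The documents do not support this. The Sample size calculation assumes 12% under standard therapy, so guideline co-treatment is nominally inside that figure. The cited range of 7.3% to 14.1% is for hospitalised patients in general and is not an effect of antibodies or plasma. Splitting mortality by co-treatment would also tell little: at the expected 2%, 58 patients give 0.02 × 58 = 1.2 deaths.

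**Conclusion.** The point holds in a limited form. Viral clearance due to permitted antibodies or plasma may be credited to proxalutamide in outcomes (9) and (10) and cannot be told apart from its effect. The Discussion presents the source of this ambiguity as a strength and describes the missing control group only as a limit on generalizability.

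A reader might go further and infer that another agent's effect is in fact being credited, or that exposure was cut short in patients who responded to something else. Actual use of these agents is not reported, so neither follows.

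The size is unknown. The conclusion rests on two assumptions: some patients receive these agents, and the agents have some effect on PCR or Ct. Severity is minor: the endpoints are secondary and the trial is labelled exploratory. Recruitment of 64 is reported as complete, but analysis and reporting can still be changed.

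**What to change.** Use the concomitant-medication data already scheduled, and leave clinical management as it is.

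- **(a)** Tabulate how many patients received an anti-SARS-CoV-2 antibody or convalescent plasma, which agent, and when it started relative to day 1.
- **(b)** Report outcomes (9) and (10) as observed for all patients. As a sensitivity analysis, report them again with PCR/Ct results after the first dose of such an agent, given before or after day 1, not counted as clearance or Ct change on proxalutamide. Say in advance whether these patients stay in the denominator of (9), which gives a low figure, or leave it, which gives a smaller subset.
- **(c)** Describe the viral results as those of proxalutamide plus standard of care. Make no claim of clearance by proxalutamide from results preceded by such an agent.
- **(d)** In the Discussion, state uncontrolled co-treatment as a limit on attribution rather than a strength, and extend the control-group limitation beyond generalizability.

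The cost is some analysis wording, one extra set of tables and a few sentences of text. The downside is that the subset without co-treatment is smaller and less precise, may be selected because clinicians choose whom to treat, and is still uncontrolled. The sensitivity analysis removes one source of bias and does not establish a proxalutamide effect.

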### Study endpoints

The primary endpoint of this study is 30-day all-cause mortality. Secondary outcomes include the following:(1) 60-day all-cause mortality;(2) The proportion of clinical deterioration, which is defined as the need within 30 days after administration for admission to the intensive care unit or invasive mechanical ventilation/ extracorporeal membrane oxygenation (ECMO), or all-cause mortality;(3) Mean change in clinical status using the 8-point-ordinal-scale from day 1 (baseline) to day 15 and day 22 (optional);(4) Time to sustain clinical recovery (determined using an 8-point ordinal scale);(5) Percentage of subjects reaching sustained clinical recovery (determined using an 8-point ordinal scale) on days 5, 8, 15, and 22 (optional);(6) Mean change in the Acute Physiology and Chronic Health Evaluation II (APACHE-II) scores from day 1 (baseline) to days 15 and 22 (optional);(7) Changes in oxygenation index measured by blood gas analysis or blood oxygen saturation from day 1 (baseline) to days 3, 5, 8, 15, and 30 (optional);(8) Changes in chest CT scan (optional) from baseline to day 8 or 15;(9) Percentage of subjects confirmed negative for SARS-CoV-2 RT-PCR by nasopharyngeal (NP) swab on days 3, 5, 8, 15, and 30 (optional);(10) Change in Ct values of SARS-CoV-2 RT-PCR on days 3, 5, 8, 15, and 30 (optional);(11) Safety assessments (eg, AEs, serious AEs, and abnormal laboratory data) from the time of SARS-CoV-2 RT-PCR turned negative to day 30.

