### Follow-up and data collection

Patients will be followed-up until 60 days or death, whichever comes first. In this trial, data collection will occur on days 1, 3, 5, 8, 15, 22, 30, and 60. The schedule of data collection is shown in Table 2. Efficacy assessment includes all-cause mortality, clinical status (8-point ordinal Scale), APACHE-II scores, oxygenation index, changes in chest CT scan, and the clinical performance of nasopharyngeal severe acute respiratory syndrome coronavirus 2 reverse transcription polymerase chain reaction (NP SARS-CoV-2 RT-PCR) testing.

**Table 2 Tab2:** Schedule of patient assessments

Time Point	Screening	Treatment Period		Safety Follow-up				
		Baseline (Day 1)	Day 2-Day 7 (up to Day 14)	Day 15 ± 2	Day 22 ± 2		Day 30 ± 3	Day 60 ± 3
Informed consent	●							
Verify eligibility criteria	●							
Demographics	●	●						
Medical History	●	●						
Targeted physical exam	●	●						
Review SARS-CoV-2 results	●	●						
Review X-ray or CT if applicable	●	●						
Vaccination status	●	●						
Vital signs including SpO_2_	●	●	Once a day till discharge	●			●^a^	
Targeted Physical Examination		●	●	●				
Clinical data collection		●	●	●	●^a^			
AEs evaluation		●	Once a day till discharge	●	●		●	●
Concomitant medication review		●	Once a day till discharge	●	●		●	
X-ray or CT			●^a^	●^a^				
12-ECG	The decision is made by professional investigators							
Hematology, urine routine, and coagulation action test	●	●	Day 3, 5, 8 (all ± 1 day)	●		●		
Pregnancy test for females of childbearing potential	●					●		
Nasopharyngeal swab		●	Day 3, 5, 8 (all ± 1 day)	●		●^a^		

*AEs* adverse events, *CT* computed tomography, *ECG* electrocardiography, *PI* principal investigator, *SARS-CoV-2* severe acute respiratory syndrome coronavirus 2

^a^ optional; ● mandatory

The safety assessment includes general vital signs, physical examination, 12-lead electrocardiography (ECG), laboratory examination (routine blood test, blood biochemical, routine urine test, and biomarker analysis) chest radiography, CT scans, and AEs. The physical examination includes assessments of the eyes, ears, nose, mouth, throat, cardiovascular, respiratory, gastrointestinal, genitourinary, hematologic/lymphatic, endocrine, and neurological.

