The 8-point ordinal scale is an assessment of the clinical status at the first assessment of a given study day. The scale is defined as follows: (1) Death; (2) Hospitalized, on invasive mechanical ventilation or ECMO; (3) Hospitalized, on non-invasive ventilation or high flow oxygen devices; (4) Hospitalized, requiring supplemental oxygen; (5) Hospitalized, not requiring supplemental oxygen- requiring ongoing medical care (COVID-19 related or otherwise); (6) Hospitalized, not requiring supplemental oxygen, and no longer requires ongoing medical care; (7) Not hospitalized, limitation on activities; (8) Not hospitalized, no limitations on activities [21].

APACHE II score is a severity score and mortality estimation tool developed from a large sample of ICU patients, which consists of an acute physiology score (APS), the age of the patient, and chronic health points. And APACHE II score is made of 12 physiological variables and 2 disease-related variables. The maximum APACHE-II score is 71, though it is rare for a patient to score higher than 55. When APACHE II scores are combined with an accurate description of the disease, they can prognostically stratify acutely ill patients and assist investigators in comparing the success of new or differing forms of therapy [22, 23].

Nasopharyngeal swabs will be performed following a standardized procedure in this trial [24]. In addition, the result of NP SARS-CoV-2 RT-PCR will be adopted, if patients have already tested for NP SARS-CoV-2 RT-PCR no more than 48 h before the first drug administration. The viral clearance of COVID-19 in the treatment period defines as the results of both tests (the first test and retested 24 h later) being negative SARS-CoV-2 RT-PCR test or Ct values > 35.

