### Statistical analysis

All efficacy analysis results are analyzed in the full analysis set (FAS) and per-protocol set (PPS). The FAS is defined as all randomized patients who received at least one dose of the study drug. The PPS is defined as all patients who completed the treatment without serious violation of the protocol. The safety analysis will be performed based on the FAS and no imputation will be made for missing safety data. Categorical data will be expressed as numbers and percentages, and quantitative data will be expressed as means ± standard deviation (SD), median, interquartile range (IQR) values, or minimum and maximum. The primary outcome will be an analysis of the percentage of 30-day all-cause mortality. The analysis of efficacy in the secondary endpoint measures will be based on their variable attributes in an appropriate way. For binary variables, the exact probability method will be used to calculate the probability of the subject with clinical deterioration. For continuous variables, the value of actual measured values and the chances from the baseline will be summarized. For rank variables such as changes in the score of the 8-point order scale, the paired Signed Rank Test method will be used. For time-to-event variables, the Kaplan–Meier method will be used to estimate the median and Kaplan–Meier graphs will be provided. All statistical analyses will be performed using Statistical Analysis System 9.4 (SAS Institute, Inc, Gary, NC), and statistical significance was set at *p* < 0.05.

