### Safety analysis

Adverse events are coded using the medical dictionary for regulatory activities (MedDRA) [27]. In this trial, statistical analysis is mainly performed for treatment-emergent adverse events (TEAEs), and pretreatment adverse events will be listed in a list. The number and proportion of all adverse events, drug-related adverse events, serious adverse events, severe adverse events, and adverse events leading to discontinuation of the drug will be calculated. Adverse events will be classified and statistically analyzed at two levels: system organ class (SOC) and preferred term (PT).

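### Secondary outcome (11) opens the safety window only when RT-PCR turns negative, so as written it mostly falls after dosing and contradicts the plan's own safety collection and analysis

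*Protocol article*

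**What the plan says.** Study endpoints, secondary outcome (11), is the only safety endpoint in the list: "Safety assessments (eg, AEs, serious AEs, and abnormal laboratory data) from the time of SARS-CoV-2 RT-PCR turned negative to day 30".

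The Intervention section gives three ways for dosing to end:
- By duration: "The duration of the study treatment will last for 7 days and can be extended to 14 days".
- By PCR, where a first result that is negative or has Ct > 35 is followed by a second: "repeated testing is still negative or Ct values > 35 after 24 h, the treatment will be discontinued by the investigator".
- By toxicity: "If grade 3–4 drug-related adverse events (AEs) occur during treatment, proxalutamide will be permanently discontinued".

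Three other places describe safety without any PCR condition:
- Table 2 (Follow-up and data collection) has AEs evaluated at baseline on day 1, then during treatment "Once a day till discharge", then on days 15, 22, 30 and 60.
- Statistical analysis: "The safety analysis will be performed based on the FAS and no imputation will be made for missing safety data". The FAS requires at least one dose.
- Safety analysis: "statistical analysis is mainly performed for treatment-emergent adverse events (TEAEs"), with counts that include drug-related events, serious events and events that led to the drug being stopped.

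**The concern.** A safety endpoint normally starts at first exposure. This one starts at a post-baseline event that is both favourable to the patient and a trigger for stopping the drug. Two consequences follow if it is applied literally. First, most of the exposure period lies outside the window, so events that arise on drug are largely not counted. Second, entry to the window is conditional on viral clearance, so patients who stay positive contribute nothing to it.

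Safety is half of the trial's stated objective, and there is no control arm, so the reported event profile is all the safety evidence the trial will give. A reader who takes the endpoint list as the prespecified definition would accept a post-clearance summary as the planned result, while the analysis sections describe something else.

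**Working it through.** No arithmetic in the plan bears on this point. The only design calculation (58 patients, 64 with drop-out) concerns mortality. The check is to lay the endpoint window against the dosing rules and then against the other safety passages.

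**Step 1: window against dosing.** The window runs from the day RT-PCR turns negative to day 30. Dosing starts on day 1. The examples below assume clearance on a scheduled swab day.

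| Patient's course | Dosing time inside the window |
|---|---|
| Clears during dosing, repeat test confirms | About the 24 h between the two tests. Example: negative on day 5, confirmed on day 6; days 1 to 4 are outside. |
| One negative, then a positive repeat | Dosing may continue with the window arguably already open, because endpoint (11) does not say whether one negative is enough. |
| First negative after a completed course | None. Example: negative on day 8 after a 7-day course; 0 of 7 dosing days are inside. |
| Stopped for toxicity while still positive | None. The event that stopped the drug precedes the window. |
| Never negative by day 30, or dies while positive | The window does not open. |

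The start point is also loosely defined. The clearance definition in Follow-up and data collection needs "the results of both tests (the first test and retested 24 h later) being negative SARS-CoV-2 RT-PCR test or Ct values > 35", and the stopping rule likewise accepts Ct > 35. Endpoint (11) says only that PCR turned negative, and mentions neither the repeat test nor the Ct threshold. A patient could meet the stopping rule on two Ct values above 35 and, on a strict reading, not yet have entered the safety window.

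**Step 2: window against the other safety passages.**

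| Aspect | Endpoint (11) | Elsewhere in the article |
|---|---|---|
| Start | PCR negativity | Day 1 (Table 2, AE row) |
| End | Day 30 | Day 60 for AEs (Table 2) |
| Patients | Those who turn negative | FAS, at least one dose (Statistical analysis) |
| Events | Those after negativity | Mainly TEAEs, including events that led to stopping the drug (Safety analysis) |

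The last row is the clearest conflict. An event that leads to stopping the drug must occur while the patient is still being dosed. Under endpoint (11) it could count only in the short overlap between a first negative and the end of dosing.

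**Step 3: how many patients.** Secondary outcome (9) reports PCR negativity as a percentage at each visit, so the plan does not assume that everyone clears. It gives no expected rate and no time distribution. The share of patients with no window could be anything from 0 to 100%.

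**The case against.** The strongest reply is that the rest of the article already does the right thing. AEs are evaluated daily during treatment until discharge, the safety analysis uses all dosed patients, and the events analysed are treatment-emergent. On that view the clause is a drafting slip in the last of eleven secondary outcomes. Much of this stands, and it limits the finding in four ways.

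- A reader might infer that on-treatment safety data are lost, or that the trial's safety profile will look falsely clean. The documents do not support that. It would follow only if endpoint (11) overrode Table 2, the FAS rule and the TEAE analysis, and nothing says that it does.
- A reader might infer that deaths escape the safety picture. They do not. All-cause mortality at 30 days is the primary endpoint, 60-day mortality is a secondary endpoint, and death is part of clinical deterioration. None of these depends on PCR.
- A reader might infer that every patient who dies is excluded. Those who clear and then die do enter the window; only those who die before turning negative do not.
- A reader might infer that the window opens exactly when dosing stops. It need not: the repeat test, a positive retest, the planned duration and toxicity all separate the two times.

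What the reply does not do is resolve the conflict. The article may contain a slip, but it does not say so, and it does not say which definition governs the reported safety result.

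**Conclusion.** The point holds as an internal contradiction in the definition of the trial's only listed safety endpoint. Read literally, endpoint (11) covers a mostly post-dosing period in patients selected by viral clearance. Table 2, the FAS rule and the TEAE analysis cover all dosed patients from day 1. Reporting safety by endpoint (11) would omit most on-treatment non-fatal AEs, serious AEs and laboratory abnormalities, and all such events in patients who never turn negative.

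The size cannot be stated as a number of patients or events, because the documents give no clearance rate. The conclusion rests on the wording of the endpoint and on the dosing rules as printed. It does not depend on any assumed clearance time; the day-5 and day-8 cases are illustrations only. Data collection, the primary endpoint and the sample size are not affected.

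**What to change.** Restate secondary outcome (11) as AEs, serious AEs and abnormal laboratory data from first dose to day 30, in all patients who received at least one dose (the FAS), regardless of PCR result, with AEs continued to day 60 as Table 2 already schedules. State the TEAE window so that it matches. The Safety analysis section uses the term without giving a window, so there is no existing definition in the article to point to. If events after clearance are of interest, report them at most as a descriptive subset, and say whether clearance there means the two-test definition.

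The cost is a sentence in the endpoint list and a matching line on the TEAE window. No new AE data are needed. Table 2 also schedules haematology, urine and coagulation tests from baseline through days 3, 5 and 8. Blood biochemistry is named only in the text below the table, so its visit days should be confirmed against the full protocol. The article reports that all 64 participants had been recruited by 16 May 2023, so the change affects analysis and reporting text only and touches no treatment rule.
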